## ***Key Secondary objective***

A second object is to analyse the primary variable with the same possible risk factors as above, but include Lymph node dissection in the model.

Item 31-33 Lymph node dissection:,yes vs no

### **CRF 6-12 weeks**

Item 51: Patient drop-out (Yes/No)

### **CRF 12 months**

Item 51: Patient drop-out (Yes/No)

### **CRF 24 months**

Item 51: Patient drop-out (Yes/No)

## ***Secondary objectives***

The estimation of the incidence of incisional hernia formation after prostatectomy is based on physician reports of surgery due to incisional hernia and patient reports on seeking health care due to suspected incisional hernia.

## **Possible risk factors for incisional hernia ?**

Age above 70

Artherosclerosis

BMI above 30

Hypertension

Previous abdominal surgery

Smoking

Diabetes

Pulmonary disease

## **HANDLING OF MISSING VALUES AND OTHER DATA CONVENTIONS**

In order to handle the issue with missing data of risk factors used in the model, multiple imputation by means of chained equations (MICE) will be used.

## STATISTICAL METHODOLOGY

### *General principles*

#### **Multiplicity**

#### **Interpretation of results**

A risk factor is here referred to as a variable that is associated with the outcome of interest. The variables specified in the previous sections are, based on clinical judgement and earlier studies, regarded as potentially clinically relevant. Interpretation of the results will consider clinical relevance of the estimated degree of association and will be cautiously addressed due to the risk of spurious and false positive associations.

#### **Sample size**

The LAPPRO study was designed with the aim to compare RALP and RRP with regard to incontinence at 12 months [9]. Groin hernia formation is a secondary outcome in that study and hence sample size is not calculated for groin hernia formation.

In a previous study[7] the incidence of inguinal hernia operation within two years after prostatectomy was approximately 6% and 7.5% for RALP and RRP (a risk ratio of 0.80), respectively. With 3706 evaluable patients (2764 and 942 with RALP and RRP, respectively) and a true incidence of 6% and 7.5%, these will be detected with approximately 35% power. However, for the endpoint used here, the incidence is expected to be higher. As illustration, with true incidences of 10% and 12.5%, respectively, a difference will be detected with 55% power using a two-sided test at 5% significance level.

#### **Demography and patient characteristics**

The following variables will be summarized and described:

- Age (median (Q1 ; Q3))
- BMI (median (Q1 ; Q3))
- Diabetes yes/no
- Cardiopulmonary disease Yes/no
- Smoking/non-smoking
- Heavy work load yes /no
- Tumour stage: low risk, and high risk
- Physical activity in history

#### **Statistical method**

The primary objective of evaluating the association between hernia incidence and operation and the evaluation of risk factor will be done simultaneously with the same statistical model. The relative risk of at least one inguinal hernia within 24 months after surgery, comparing surgical methods (RALP, RRP), will be modelled using a modified Poisson regression approach of Zou ([10]).

Except for the exposure, the surgical method (RALP, RRP), possible risk factors (age, physical workload, BMI, diabetes, pulmonary disease, smoking, hernia prior operation, physical activity and tumour size) will be evaluated by the same algorithm introduced by Bursac ("Purposeful selection of variables in logistic regression", Source Code for Biology and Medicine 2008;17). This model might also include interactions.

The key secondary objective will evaluate the same risk factors, but will include Lymph node dissection (yes/no) in the model.

The secondary objectives will be evaluated in an analogous way, using the risk factors ....

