## ANALYSIS POPULATION, TYPE OF ANALYSIS

### *Analysis population*

The entire cohort in the LAPPRO trial (n=3706), where RALP was compared with RRP. Since it is a non-randomized study patient will be analysed as-treated.

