**Low risk T1-2 vs high risk T3-4**

**BASELINE PATIENT CHARACTERISTICS, TUMOUR FACTORS, COMORBIDITIES AND RISK FACTORS ARE BASED UPON:**

### **Preoperative questionnaire**

Sociodemographics (Q4-6), BMI (Q8-9), relevant comorbidities (Q30, 35, 41, 43, 44), previous abdominal surgery (Q52), previous IH surgery (Q46, 47), smoking (Q57), physical activity (Q143), urinary flow (Q149)

Patients were dichotomized as current smoker (including pipe smoking) or non-smoker (former smoker or never smoker) according to their answer to the question “Do you smoke or have you smoked?”.

Q 143: Hur ofta har Du varit fysiskt aktivt i 30 minuter eller mer den senaste månaden..? *With a 4 point Likert scale (1= aldrig, 2=ibland (1-2 ggr/v), 3=Ofta (3-4 ggr/v), 4= Dagligen eller nästan dagligen (5-7 ggr/vecka)) The answers will be dichotomized with a cut-off point between 2 and 3 prior to analysis.*

Q 146: Hur ofta har Du varit tvungen att trycka på eller krysta för att börja kissa den senaste månaden? *With a 6 point Likert scale (1=aldrig, 2=färre än 1 av 5 vattenkastningar, 3=färre än hälften av vattenkastningar, 4= ungefär hälften av vattenkastningar, 5= fler än hälften av vattenkastningar, 6=alltid). The answers will be dichotomized with a cut-off point between 3 and 4 prior to analysis.*

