## ***Covariates, stratum and subgroups***

No additional variables apart from the variables that will be evaluated for risk factors will be included as covariates in the statistical model.

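### The adjustment set for the primary RALP vs RRP relative risk is chosen from the outcome data, with unnamed interactions allowed; this can leave residual confounding and an interval that under-covers

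*SAP*

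**What the plan says.** All references are to the SAP.

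- **Analysis population:** "Since it is a non-randomized study patient will be analysed as-treated".
- **Statistical method:** the primary comparison and "the evaluation of risk factor will be done simultaneously with the same statistical model". The relative risk "will be modelled using a modified Poisson regression approach". Surgical method is excepted from the search. Nine candidates (age, workload, BMI, diabetes, pulmonary disease, smoking and the rest of the list) are not: "hernia prior operation, physical activity and tumour size) will be evaluated by the same algorithm", which is purposeful selection. The section then adds: "This model might also include interactions". It names no interaction, gives no rule for admitting one, and states no entry, removal or change-in-estimate threshold.
- **Covariates, stratum and subgroups:** this section closes the list: "No additional variables apart from the variables that will be evaluated for risk factors will be included as covariates in the statistical model".
- **Interpretation of results:** promises cautious reading because associations may be spurious. It changes neither the estimate nor the interval.

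**The concern.** One model is asked to do two jobs. A search for risk factors may reasonably let the data decide which variables stay. An estimate of the technique effect in a non-randomised cohort needs its confounders decided beforehand, because the SAP names no other protection such as matching, stratification or a propensity score.

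Under the plan as written, a variable that differs between the groups and is modestly related to hernia may fail the outcome-based screen and leave the model. Its share of the confounding then goes into the RALP vs RRP relative risk, and the reported standard error takes no account of the search. If an interaction with technique were selected, the primary endpoint would have no single relative risk. The primary result is at stake, in a setting where the SAP itself expects only about 35-55% power.

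**Working it through.** **1. The SAP's own power figures (Sample size).** Inputs: 2764 RALP, 942 RRP, two-sided 5%. Power = Φ(|p1 − p2|/SE − 1.96), with SE = √[p1(1−p1)/n1 + p2(1−p2)/n2].
- 6% vs 7.5%: SE = √(0.0564/2764 + 0.069375/942) = 0.00970; 0.015/0.00970 = 1.547; power 34.0%.
- 10% vs 12.5%: SE = √(0.09/2764 + 0.109375/942) = 0.01219; 0.025/0.01219 = 2.050; power 53.6%.

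A continuity-corrected version gives 34.8% and 54.9%. The stated 35% and 55% reproduce and are not in dispute.

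**2. Is selection needed for a stable fit?** Expected events:
- 0.06×2764 + 0.075×942 = 165.8 + 70.7 = 236
- 0.10×2764 + 0.125×942 = 276.4 + 117.8 = 394

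Technique plus nine covariates at one parameter each is 10 parameters: 236/10 ≈ 24 and 394/10 ≈ 39 events per parameter. Without workload: 236/9 ≈ 26 and 394/9 ≈ 44. Selection is not needed for stability.

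**3. Simulation A.** n = 3706, about 25% RRP, RRP incidence about 12.5%, nine covariates, robust Poisson, technique forced in, 2000 runs per setting (Monte Carlo error about 0.5 points at 95% coverage). Assumed, because the SAP does not give them: univariable p<0.25, removal at p>0.10 unless a coefficient changes by more than 20%, re-entry at p<0.15, no interactions, no missing data, and four confounding patterns.

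| Pattern | True RR | Coverage, selected | Coverage, full | Bias in log RR, selected | SE selected / full | True confounders dropped |
|---|---|---|---|---|---|---|
| Weak | 1.0 | 94.5% | 95.6% | 0.012 | 0.1044 / 0.1063 | 32% |
| Weak | 0.8 | 94.6% | 95.3% | 0.019 | 0.1079 / 0.1107 | 43% |
| Mainly prior hernia and age | 1.0 | 94.6% | 95.4% | −0.003 | 0.0941 / 0.0954 | 42% |
| Mainly prior hernia and age | 0.8 | 94.5% | 95.3% | −0.005 | 0.0980 / 0.0997 | 49% |
| Moderate, same direction | 1.0 | 93.3% | 95.1% | 0.022 | 0.1064 / 0.1079 | 26% |
| Moderate, same direction | 0.8 | 94.8% | 95.5% | 0.034 | 0.1098 / 0.1123 | 37% |
| Strong | 1.0 | 87.8% | 95.0% | 0.039 | 0.1057 / 0.1106 | 37% |
| Strong | 0.8 | 93.1% | 95.1% | 0.060 | 0.1088 / 0.1164 | 50% |

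- Bias in the full model is below 0.002 throughout.
- Worst bias after selection: 0.80 × e^0.060 ≈ 0.85. The shift of 0.060 is 27% of |ln 0.80| = 0.223.
- The selected model's SE is 1.4% (0.0941/0.0954) to 6.5% (0.1088/0.1164) below the full model's. Against its own run-to-run spread the shortfall is larger in one setting (strong, RR 1.0): 0.1057/0.1203 = 0.88.
- Without the change-in-estimate step, coverage was 86.1-94.6%.
- With no adjustment at all, coverage was 24-88%.

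**4. Sensitivity to the assumed confounding, same thresholds.**
- *Simulation B*: 4000 runs, true RR 1.0, all nine covariates weak confounders (outcome RR 1.05-1.07 and log-odds of technique 0.2-0.3 per SD). Type I error 7.0%, 9.9% and 11.4% after selection, against 4.7%, 4.9% and 4.7% in the full model.
- *Simulation C*: 1200 runs, true RR 1.0, outcome RR 1.06, log-odds 0.25. Type I error, selected vs full: all nine aligned 7.0% vs 4.3%; alternating signs 5.8% vs 4.3%; random signs 6.9% vs 5.4%; only three of nine linked to technique 4.9% vs 4.3%.
- *Simulation D* (600 runs per setting, thresholds likewise assumed): all nine aligned, coverage 92-95% with log-RR bias 0.03-0.05, against 95-96% and at most 0.01 in the full model. With mixed signs or only three confounders, coverage 93-95% with bias 0.01-0.02.

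**5. Interactions.** Screening nine technique-by-covariate terms at an assumed 5%, taken as independent: 1 − 0.95^9 = 37% chance of at least one false positive.

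**The case against.** The strongest case on the other side has five parts.

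- **The harm is conditional.** The SAP shows no imbalance between the groups and states no thresholds. With weak confounders, mixed signs or few variables linked to technique, coverage stays close to nominal. This stands: a reader might infer that selection will drop real confounders and will make the interval too narrow, but the document does not support that as a certainty. The type I error of 7.0-11.4% in simulation B comes from unfavourable scenarios and is not a general range.
- **Width is a small part.** The SE falls by only 1-7% relative to the full model, and when confounders are aligned much of the excess error is residual bias. This also stands.
- **Technique is exempt from selection, and cautious interpretation is promised.** True, but neither fixes the adjustment set nor corrects the interval.
- **No technique interaction is named.** True. The loss of a single relative risk arises only if one is selected; the text permits it without a rule.
- **Other baseline variables.** A reader might infer that the SAP wrongly bars previous abdominal surgery, ASA class, PSA and Gleason score. It collects them as baseline data, but lists previous abdominal surgery as a risk factor only for incisional hernia and does not tie the other three to inguinal hernia. Their omission is not shown to be an error.

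**Conclusion.** The point holds as a conditional risk to the primary estimate. The text settles that the adjustment set for the RALP vs RRP relative risk is chosen from the outcome data, that no confounder is fixed in advance, and that interactions are open. How much this harms the estimate is not settled. In simulation A coverage after selection ran from 94.8% down to 87.8%, against 95.0-95.6% with all nine covariates forced in, with a log-RR bias of up to 0.060. Those figures rest on assumed thresholds and confounding patterns, complete data and no interactions. All four simulations agree in direction: the prespecified full model did as well or better. As it is also affordable at the SAP's own incidences, the change should be made; the evidence does not show that the planned analysis must be wrong.

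**What to change.** Split the model in the Statistical method section.

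1. **Primary objective:** one prespecified modified Poisson model with technique plus the SAP's listed preoperative factors, with no selection and no interactions.
2. **Physical workload:** its item definitions appear only in the 3-, 12- and 24-month questionnaires. Include it only if a preoperative measure exists, and name the item; otherwise leave it out of the primary model.
3. **Risk-factor objective:** keep purposeful selection, labelled exploratory, and state its thresholds and how it is applied across the multiply imputed data sets.
4. **Interactions:** report any technique interaction separately from the primary relative risk.
5. **Optional:** a sensitivity analysis adding previous abdominal surgery, ASA class, PSA and Gleason score. With 14 parameters this still leaves 236/14 ≈ 17 to 394/14 ≈ 28 events per parameter.

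Cost: SAP wording, one extra model fit, and a primary SE a few percent larger (in simulation A from 0.1079/0.1064, about 1%, to 0.1164/0.1088, about 7%).

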## LIST OF TABLES AND FIGURES PLANNED FOR THE MANUSCRIPT

Figure 1: Flow chart of included patients

Table 1: Patient characteristics and demography.

Table 2 Multivariate analyses

